## Abstract

**Background:**

Based on a recent meta-analysis, a continuous suture technique with a suture to wound length ratio of at least 4:1, using a slowly absorbable monofilament suture material, is recommended for primary median laparotomy closure. Incisional hernia, which develops in 9 to 20% of patients, remains the major complication of abdominal wall closure. Current clinical data indicate that the incidence of incisional hernias increases by 60% between the first and the third year after median laparotomy, implicating that a follow-up period of 1 year postoperatively is too short with regard to this common complication. Trauma to the abdominal wall can be reduced by improvements in suture technique as well as suture material. Several factors, such as stitch length, suture tension, elasticity, and tensile strength of the suture material are discussed and currently under investigation. A Swedish randomized controlled trial showed a significant reduction in the incisional hernia rate by shortening the stitch length. However, a non-elastic thread was used and follow-up ended after 12 months. Therefore, we designed a multicenter, international, double-blinded, randomized trial to analyze the influence of stitch length, using an elastic, extra-long term absorbable monofilament suture, on the long term clinical outcome of abdominal wall closure.

**Methods:**

In total, 468 patients undergoing an elective, median laparotomy will be randomly allocated to either the short stitch or the long stitch suture technique for abdominal wall closure in a 1:1 ratio. Centers located in Germany and Austria will participate. The primary endpoint measure is the incisional hernia rate 1 year postoperatively, as verified by ultrasound. The frequency of short term and long term complications as well as costs, length of hospital stay and patients’ quality of life (EQ-5D-5 L) will be considered as secondary parameters. Following hospital discharge, patients will be examined after 30 days and 1, 3, and 5 years after surgery.

**Discussion:**

This study will provide further evidence on whether a short stitch suture technique in combination with an elastic, extra-long term absorbable monofilament suture can prevent incisional hernias in the long term, compared with the long stitch suture technique.

**Trial registration:**

NCT01965249.

## Background

The risk of developing an incisional hernia after primary elective median laparotomy is reported in the literature as being between 9 and 20% [1]. Among multiple risk factors, the malfunction or delay of collagen synthesis appears to be of utmost relevance. Friedman *et al.* [2] showed direct correlation between a reduced collagen I/III quotient and the development of an unstable scar, based on immature, less mechanically stable, collagen 1. Obesity, steroid therapy, malnutrition, nicotine use, and connective tissue diseases are undeniably further main risk factors. But how should other factors, such as closure technique, suture material, or surgical experience, be interpreted in this context? Despite the paradigm shift in hernia surgery triggered in the beginning of the 1980s, which was initiated with the first documented use of plastic meshes by Usher [3], the problem of ensuring appropriate closure of the median laparotomy has not yet been satisfactorily solved. This issue still remains a topic of controversial discussion.

Since the publications of the Swedish group of Leif Israelsson [4,5] in 1993, the continuous closure technique with a defined suture/wound length ratio of 4:1 has increasingly been used [4,5]. For a long time, discussions regarding the ideal suture revolved around whether it should be ‘non- or slowly absorbable’. After numerous studies and meta-analyses [6-8], conducted most recently by Diener *et al.* [9], the evidence for the ideal primary abdominal closure seem to have been adequately established. Based on the most recent meta-analysis of primary laparotomy closure, the continuous suture technique with a suture to wound length ratio of at least 4:1, using a monofilament, slowly absorbable suture can be considered state of the art.

Minimization of trauma to the abdominal wall is the most important consideration in terms of improvement of surgical technique and suture material used. According to the biomechanical principles of abdominal wall tension, the distribution of suture tension over small tissue bridges using the appropriate needle size and suture strength to minimize tissue trauma is the most promising approach [10]. In addition to the surgical technique, the elasticity of the suture material is a further critical factor in preventing so-called ‘buttonholes’, according to physiological studies of the abdominal wall. Taking into account the results of experimental studies by Höer *et al.* [11,12], the association of different closure techniques and abdominal wall perfusions leading to different collagen ratios seems to be crucial in terms of creating a stable scar.

Based on these facts, the use of a monofilament suture material with a high elasticity in combination with a long-lasting basic retention strength as well as an extra-long absorption time of 390 days (MonoMax®, B. Braun Surgical SA, Rubi, Spain) seems to bear a significant potential for the improvement of abdominal wall suture stability [13]. This suture material might further improve the promising results of Millbourn’s randomized controlled trial [14] and will, therefore, by used in our multicenter, randomized controlled trial, which is aimed at comparing the long term clinical outcome of small versus large bite closure techniques after primary median laparotomies.

## Methods

### Study design

The Effect of Suture Technique on the Occurrence of Incisional Hernia (ESTOIH) study is a prospective, international, multicenter, double-blinded, randomized controlled trial, aimed at evaluating the efficacy of the short stitch suture technique using an elastic, extra-long term absorbable monofilament suture (MonoMax®) after primary median laparotomy, in comparison with the long stitch suture technique.

In total, 468 patients will be enrolled in seven centers located in Germany and Austria. Patients will be randomly allocated to receive either the short or the long stitch suture technique for abdominal wall closure in a 1:1 ratio. The surgical procedure used to close the abdomen will be standardized in both suture technique groups and the participating centers will be trained in the different suture techniques.

After the operative procedure, the investigator will examine the patients on the second day after surgery, on the day of discharge, and at 30 days ±10 days, 1 year ±1 month, 3 years ±3 months and 5 years ±3 months postoperatively. Patients and observers performing the follow-up visits will be unaware of the suture technique (double-blinded) used. The study will last 5 years for each patient (Figures 1 and 2).

**Figure 1 Fig1:**
[figure not shown]
**CONSORT flow chart.**

**Figure 2 Fig2:**
[figure not shown]
**SPIRIT diagram.** SPIRIT, Standard Protocol Items: Recommendations for Interventional Trials.

### Participants

Patients at least 18 years of age undergoing an elective primary median laparotomy, with an incision length of ≥15 cm and an expected survival time longer than 1 year, and with an American Society of Anesthesiologists (ASA) status of I to III are eligible for this trial. After approval of the study protocol by the local ethics committee, patients will be screened consecutively for possible eligibility in the participating centers. All patients who seem to meet the in- and exclusion criteria will be asked whether they are willing to participate in the ESTOIH study and will be informed about the purpose of the trial. Written informed consent has to be obtained from each enrolled patient before the operation.

Exclusion criteria are:Emergency surgery,Body mass index ≥30 kg/m^2^,Pancreatic tumor patients,Patients who will be operated on owing to an abdominal aortic aneurysm,Peritonitis,Coagulopathy,Current immunosuppressive therapy (more than 40 mg of a corticoid per day or azathioprine),Chemotherapy within 2 weeks before operation,Radiotherapy of the abdomen within 6 weeks before operation,Pregnant women,Severe neurologic and psychiatric disease,Lack of compliance.

### Randomization

Eligible patients will be randomly allocated to receive either the short or the long stitch suture technique in a 1:1 ratio by opening a sealed opaque envelope. Envelopes are supplied by the sponsor, according to a randomization list provided by a statistician using the statistical software SAS 9.1. A separate randomization list was prepared for each participating center, to avoid center-specific effects and to assure a balanced distribution of both treatments within one center (stratification). Random blocks of different lengths were used. The randomization lists are sealed and locked up at the sponsor site. The envelopes will be assigned to the patients in chronological order by a surgeon, according to a consecutive random number.

Each envelope contains the device (suture material for the indented suture technique) as well as the information about which stitch technique should be applied for abdominal wall closure. Randomization is performed intraoperatively and briefly before abdominal wall closure. After randomization, each patient obtains a unique randomization number. The study site confirms the randomization result by sending a fax to the sponsor.

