### Sample size calculation

The ISSAAC study has shown a risk of 19% of developing an incisional hernia within one year using MonoMax® suture material and a long stitch technique for abdominal wall closure of a primary elective midline laparotomy [14]. The aim of this study is to demonstrate that the short stitch suture technique with MonoMax® will decrease the incisional hernia rate after 1 year by 50% compared with the long stitch technique (primary endpoint). Considering hernia rates of 19% and 9.5% in both groups, a total sample size of 424 patients (212 per group) will be necessary to detect this difference with a power of 80% and an alpha of 5%. Including a drop-out rate of 10%, a total of 468 patients will be randomized in the current study. Thus, each of the seven participating centers should recruit about 67 patients. To avoid center effects, a maximum of 200 patients may be recruited per center. Withdrawn patients will not be replaced.

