### Primary endpoint

The study hypothesis will be tested by a two-sided chi square test for independent proportions.

The hernia rate is calculated as a Kaplan-Meier estimate for the failure rate at the end of the observation period (1 year ± 1 month). The Kaplan-Meier estimate has the benefit of additionally taking into account the results of drop-out patients. For each hernia, the date of its first observation must be documented to provide a correct estimate. The date of hernia detected by ultrasound at a follow-up examination will be set to the examination date; this may lead to a slight over-estimation of the hernia rates in both groups.

Analyses will be performed according to the intention-to-treat principle. The consistency of the results will be tested by per-protocol analysis (sensitivity analysis).

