### Secondary endpoints

Secondary endpoints will be tabulated as frequencies and rates, or as means and standard deviations, as appropriate. Confidence intervals will be used when appropriate.

The two-sided chi square test for independent proportions will be used for proportion comparisons. The Kaplan-Meier method will also be used to calculate other rates to be analyzed. For each such event, the date of occurrence must be recorded. The two-sided *t* test for independent samples will be used for comparisons with continuous variables.

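### Randomisation is stratified by centre but the confirmatory chi-square test has no centre term; if hernia rates differ between centres, the test is slightly conservative and stratifying it is a free, minor gain

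*Protocol article*

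**What the plan says.** Under Randomization, the article states: "A separate randomization list was prepared for each participating center". Blocks of varying length are used, and the stated purpose is "to avoid center-specific effects and to assure a balanced distribution of both treatments within one center (stratification"). The Sample size calculation section returns to centre: "To avoid center effects, a maximum of 200 patients may be recruited per center".

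The Primary endpoint part of the statistical analysis fixes the confirmatory test: "The study hypothesis will be tested by a two-sided chi square test for independent proportions". The same part adds: "The hernia rate is calculated as a Kaplan-Meier estimate for the failure rate at the end of the observation period". Neither statement mentions centre.

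For the secondary endpoints, which are exploratory, the article says "The two-sided chi square test for independent proportions will be used for proportion comparisons", with a t "test for independent samples will be used for comparisons with continuous variables". No analysis in the article names centre as a stratum or covariate.

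**The concern.** The design treats centre as a possible source of variation in two places, and the named analysis then leaves it out. This is not a detail left to an analysis plan, because the article itself names the confirmatory test.

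The plain chi-square test treats each arm as one simple random sample. Here each centre contributes nearly equal numbers to both arms, so a high-risk centre raises both arms together and its effect largely cancels from the difference. The plain variance does not credit that cancellation. If centre predicts hernia, the variance is overstated: the test rejects too rarely under the null and gives away a little power under the alternative. The recruitment cap limits how far one centre can dominate (200/468 = 43%), but it does not remove differences between centres.

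The stake is modest. The planned power sits just above 80%, so precision that needs no extra patients is worth taking. No false-positive risk is created.

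**Working it through.** **1. The plan's own figure.** Inputs from Sample size calculation: 19% versus 9.5%, two-sided alpha 5% (the primary test is two-sided), power 80%, 1:1 allocation. The pooled rate is 0.1425.

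n per arm = [1.960 × √(2 × 0.1425 × 0.8575) + 0.842 × √(0.19 × 0.81 + 0.095 × 0.905)]² / 0.095²
= (0.969 + 0.412)² / 0.009025 = 211.4, rounded up to 212.

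This matches the stated 212 per group (424 in total), with power 80.1% at 212. The planned test and sample size agree with each other, and neither uses centre.

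**2. Why the plain variance is too large.** If centre c has rate p_c, and the mean over equal centres is p, the mean within-centre variance is p(1−p) − Var(p_c). The plain test uses p(1−p). The SE ratio, plain to stratified, is therefore √{p(1−p) / [p(1−p) − Var(p_c)]}.

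Worked example, with the spread assumed: seven equal centres at 10, 13, 16, 19, 22, 25 and 28%, the same in both arms (null case).
- p = 0.19 and p(1−p) = 0.1539.
- Var(p_c) = 0.0036.
- Ratio = √(0.1539 / 0.1503) = 1.012.
- True type I error = 2 × [1 − Φ(1.960 × 1.012)] = 4.7%.

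Simulation of this 10–28% spread (seven centres of 30 per arm) also gives 4.7% for the plain test and 5.0% for the Cochran-Mantel-Haenszel (CMH) test. With a common odds ratio bringing the mean rate down to 9.5%, power is 80.5% and 81.0%.

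**3. A range of spreads.** 40,000 simulated trials per scenario, 212 per arm in seven centres, rates of 19% and 9.5% for power and 14.25% in both arms for type I error. The between-centre SD on the logit scale is assumed, because the documents give none. Centre sizes are either near-equal (30 to 32 per arm) or unequal (100, 40, 25, 17, 12, 10 and 8 per arm, so the largest is at the cap of 200).

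| Centre sizes | Logit SD | SE ratio | Type I, plain / CMH | Power, plain / CMH |
|---|---|---|---|---|
| Equal | 0 | 1.00 | 5.1% / 5.1% | 81.0% / 81.0% |
| Equal | 0.5 | 1.01 | 4.7% / 5.0% | 80.9% / 81.5% |
| Equal | 1.0 | 1.05 | 4.1% / 5.1% | 80.9% / 83.2% |
| Unequal | 0 | 1.00 | 4.7% / 4.8% | 80.8% / 80.8% |
| Unequal | 0.5 | 1.01 | 4.7% / 4.9% | 80.5% / 81.0% |
| Unequal | 1.0 | 1.04 | 4.1% / 4.9% | 79.1% / 81.3% |

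The Monte Carlo standard error is about 0.1 point for type I error and 0.2 point for power.

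**4. Does prior short-stitch experience show the loss?** The Implementation section says that surgeons in three of the seven centres had already used the short stitch. That would plausibly act on the short-stitch arm. Assume 19% in every long-stitch arm, and short-stitch rates of 5% in three centres and 12.9% in four: (3 × 5 + 4 × 12.9)/7 = 9.5%. With 30 per arm per centre, power is 80.2% plain and 80.4% CMH, with an SE ratio of 1.00. Under a wider split of 3% and 14.4%, it is 80.6% and 80.8%. This mechanism costs almost nothing.

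**The case against.** The strongest reply is that nothing here is wrong enough to matter. The blocked lists deliver balance within centres whatever the analysis, so the stated purpose of stratifying is met. The plain test is valid and errs on the safe side. The sample size was computed for that very test and reproduces exactly. The Implementation section also describes steps that should shrink centre differences: training at every centre, suture from a single batch and common measuring equipment. All of this stands, and it is why the point is minor.

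Four stronger readings are tempting, and the documents do not support them.

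- *A reader might infer that the intervals are too wide.* That holds only if hernia rates differ between centres, and no such rates are given. Up to a logit SD of 0.5 the SE ratio is at most about 1.01.
- *A reader might infer that the experience gap between centres proves the loss.* Step 4 shows that it does not. The loss comes from differences in underlying risk shared by both arms, for which the documents give no figures.
- *A reader might infer that the trial is underpowered or that its false-positive rate is inflated.* Type I error is at or below nominal. Simulated power for the plain test stays close to the planned 80%; the lowest value, 79.1%, needs both very unequal centres and the largest assumed spread.
- *A reader might infer that every test must be stratified.* The secondary endpoints are exploratory, so this is a preference.

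One practical objection also stands. The article uses a Kaplan-Meier rate so that patients who drop out contribute. A binary CMH test does not handle censoring, so the stratified analysis has to be reconciled with that choice.

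**Conclusion.** The point holds as a minor, free improvement to the primary analysis. Allocation is stratified by centre and the confirmatory test is not; both are stated in the article. If centres differ in hernia risk, the planned test is slightly conservative. Across assumed between-centre SDs of 0 to 1.0 on the logit scale, the standard error is 0 to 5% too large, type I error is about 4 to 5% against a nominal 5%, and 0 to about 2 power points are lost. Without centre differences there is nothing to gain.

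The mismatch and its direction are certain. The size rests wholly on assumed spreads. The stated sample size and its 80% power are not called into question, and no bias is involved.

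**What to change.** Before any comparison by arm, name a centre-stratified primary comparison in one of two forms:

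- a CMH test stratified by centre, with a stratified (Mantel-Haenszel) risk difference and 95% CI, stating how patients without a one-year assessment are counted; or
- to keep the Kaplan-Meier handling of drop-outs, the difference in one-year Kaplan-Meier rates within each centre, combined across centres with a 95% CI and the corresponding test. Weights should depend on centre size and not on inverse variance. At 9.5%, a centre with 30 patients per arm expects 30 × 0.095 = 2.85 hernias in the short-stitch arm and has a 0.905^30 = 5% chance of none, which would give an estimated variance of zero.

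Keep the plain chi-square test as a sensitivity analysis and leave the sample size at 424 evaluable and 468 randomised. Stratifying the exploratory secondary tests, and showing results descriptively by prior short-stitch experience, are optional.

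The cost is a short paragraph in the plan. No new data are needed, because the first two digits of the randomisation number already identify the centre (Ethical and legal issues), and seven strata averaging about 67 patients are manageable.

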### Blinding

The treatment allocation is double-blinded. The patient and the observer responsible for the assessment of the clinical outcome will be unaware of the stitch length used for closing the midline and will have no access to the case report form. To document the clinical outcome of each follow-up examination, the sheets will be handed to the observer by an independent person (for example, a study nurse). The surgeons cannot be blinded because they have to know which suture length has to be applied for midline closure.

### Interventions

In both study groups, the abdominal wall closure will be performed using MonoMax® suture material (B. Braun Surgical SA, 08191 Rubi, Spain), an elastic, extra-long term absorbable, monofilament suture made of poly(4-hydroxybutyrate). In the long stitch group, a MonoMax® USP 1 loop in combination with a HR 48 needle will be used, and in the short stich group, a MonoMax® USP 2/0 single thread will be used in combination with a HR 26 needle. Details of the suture technique are shown in Table 1.

**Table 1 Tab1:** **Comparison short stitch versus long stitch suture technique**

**Parameter**	**Long stitch technique**	**Short stitch technique**
**Suture material**		
Product	MonoMax®	MonoMax®
USP size	USP 1	USP 2/0
Length of thread	150 cm loop	150 cm single thread
Needle	HR 48	HR 26
**Suture technique**		
Stitch interval	10 mm	5 mm
Distance from median wound incision to stitch site	10 mm	5 to 8 mm
Suture length/wound length ratio	4:1	≥5:1
Suture technique	Continuous	Continuous

The surgical procedure is carried out as usual and according to local standards regarding the indication for intervention. During all operations, the umbilicus has to be completely dissected from the linea alba for an adequate abdominal wall closure. The linea alba is prepared free from fat and cut precisely in the middle. In the case of a deviation, this is recorded in the randomization fax. After abdominal wall closure, refixation of the umbilicus is achieved using an absorbable suture and in interrupted suture technique.

The following parameters are recorded and measured in both treatment groups:Length of the wound (cm),Number of threads used,Length of the remaining suture material (cm),Number of applied stitches,Duration for abdominal wall closure (defined as the time period from the first placement of the needle through the tissue until the last knot has been closed and the thread is cut).

Using these data, the suture length used to close the midline will be calculated, as well as the suture length to wound length ratio. The number of stitches will be analyzed in accordance with the wound length and the length of the implanted suture material. The distance between the stitches can be determined as well as the lateral distance from the incision.

### Implementation

Before the start of the trial, an initiation visit was paid to each center by the study management to inform and instruct the involved personnel on the study specific documents and procedures. To standardize both suture techniques, each participating center has been trained by presentations and videos; in addition, a practical workshop took place during the first study meeting. In three of the seven centers, surgeons had already used the short stitch technique before the start of the trial and have attended a hospitation conducted by the coordinating investigator in the Wilhelminenspital in Vienna, Austria. The other four centers were instructed during a visit by the coordinating investigator [name] before the first inclusions. All study centers were provided with suture material from the same batch, with the same type of stop watch for time measurement, a counter to enumerate the stitches, and rulers to measure the wound length, to standardize this equipment within the different centers.

